### Study objectives

1.2

The *primary objective* of the study is to investigate the correlation between the degree of LA and LV fibrosis quantified by cardiac magnetic resonance (CMR), inflammatory biomarkers, and the risk of AF recurrence post catheter ablation.

The *secondary objective* of the study is to investigate the correlation between structural remodeling of the left and right atrium, epicardial fat tissue volume and serum inflammatory biomarkers in patients with AF undergoing successful catheter ablation and their impact on long term outcomes.

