### Study population

2.3

The study will include 100 subjects with AF suitable for catheter ablation. Imaging biomarkers and laboratory analyses such as: high sensitive C Reactive Protein (hsCRP), matrix metalloproteases (MMPs), interleukin-6 (IL6) and N-Terminal Pro–B-Type Natriuretic Peptide (NT pro-BNP) will be determined in the first 24 hours after the procedure. The anatomy of pulmonary veins, atrial fibrosis, atrial volumes and the amount of epicardial fat will be evaluated and quantified with late gadolinium-enhancement cardiac magnetic resonance (LGE-CMR). All these parameters will be investigated in patients with successful ablation of AF, who will be divided into 2 groups: group 1 – patients who develop AF recurrence at 1 year, and group 2 – patients with no recurrence of AF at 1 year. In all patients, the following biomarkers will be determined: serum levels of inflammatory biomarkers and NT-proBNP at 24 hours and 1-year post procedure, the amount of myocardial fibrosis at the level of left atrium and left ventricle at baseline +/− 7 days, and the amount of epicardial fat surrounding left atrium, right atrium and the entire heart at baseline +/− 7 days.

The study will be conducted over a period of 2 years, in which patients will be examined at baseline, and will be followed-up for recurrence of AF, as shown by the FIBRO-RISK diagram with the flowchart that will be used in the study (Fig. 1).

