#### Late gadolinium-enhancement cardiac magnetic resonance

2.6.3

All CMR examinations will be performed with an 1.5 T Siemens Magnetom Aera magnetic resonance equipment (Siemens, Erlangen, Germany). LV function will be assessed using cine sequences in long-axis (2-chamber and 4-chamber) and short axis. Short-axis volumetry will be used for determination of LV mass, LV ejection fraction, LV end-diastolic volume (LVEDV) and end-systolic volume (LVESV). Ventricular and atrial fibrosis will be assessed using late postgadolinium myocardial enhancement sequences (LGE) at 10 minutes after intravenous injection of gadolinium extracellular contrast agents. Acquired LGE images will be post-processed using the Medis QMass 8.1 software (Medis, Leiden, the Netherlands) with definition of the epicardial and endocardial contours and manual setting of the hyper-enhancement threshold for the recorded sequence of slices. Delayed signal intensity (DSI) analysis performed in 10 to 12 consecutive short-axis LGE images. The full width at half maximum will be used for image segmentation, using an automated hyper-enhancement threshold and fibrotic areas will be considered those with slow washout kinetic.

Quantification of epicardial fat volume will be performed by tracing and manually adjusting epicardial contours, as part of the post-processing protocols.

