#### Ablation protocol

2.6.4

Seldinger technique will be used for venous access, with 1 sheath positioned on the left and 2 sheaths on the right femoral veins. A decapolar diagnostic catheter will be placed in the coronary sinus, after being advanced via left femoral access site and secured with a 6F sheath.

Transesophageal echocardiography will be used to guide interatrial septal puncture. A bolus of 5000 to 7500 U of heparin followed by 1000 to 2000 U/h will be administrated and the following heparin dosage will be adjusted using activated clotting time, determined every 15 to 30 minutes.

In case of radiofrequency ablation, 1 non-steerable sheath will be used for placing the duodecapolar mapping catheter (Lasso) and the other steerable sheath for placing the 3.5 mm tip externally irrigated contact force-sensing ablation catheter. A continuous heparinized saline wash of the long sheaths will be provided during the entire procedure. The 3-D electro-anatomical map will be acquired with the EnSite^TM^ NavX^TM^ system, Model EE3000 (St. Jude Medical, St. Paul, MN, USA), improved by fusing images acquired with CMR images. After inserting the mapping catheter in the ostium of the pulmonary vein (PV), radiofrequency catheter ablation will be performed to obtain pulmonary vein isolation. Ablation will consist in applying a 30 W energy and a 10 to 30 g pressure with temperature adjusted at 50°C, by an irrigated (5–20 ml/min) contact force-sensing catheter positioned on the left atrial wall. A PV will be considered electrically isolated by eliminating all electrical potentials, or by demonstrating successful PV potential dissociation.

In case of cryoablation procedure, a cryoablation balloon (Arctic Front Advance Cryoablation Catheter, Medtronic, Quebec, Canada) will be advanced with transesophageal control via transseptal route and will be placed at the ostium of each pulmonary vein, delivering minus 40 to 70° cooling energy, during 180 to 240 seconds application. The ablation will be considered efficient when complete electrical block between atrial tissue and pulmonary vein will be achieved.

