### Participation timeline

2.9

**Baseline (day 0)**oObtain and document consent from participant on study consent form.oVerify inclusion/exclusion criteria.oObtain demographic information, medical history, medication history, alcohol and tobacco use history.oRecord results of physical examinations and 12-lead ECG.oCollect blood specimens (complete blood count, biochemistry and inflammatory biomarkers).oImaging procedures: transthoracic 2-D echocardiography, late gadolinium-enhancement CMRoCatheter ablation (radiofrequency or cryoablation)**Follow-up visits (month 1,3,6)**oRecord results of physical examinations, 12-lead ECG and medical history.oImaging procedures: transthoracic 2-D echocardiography**Final study visit (month 12)**oRecord results of physical examinations, medical history,12-lead ECG and determination of serum levels of inflammatory biomarkers and NT-proBNPoImaging procedures: transthoracic 2-D echocardiographyoEnd-point evaluation.

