Beside baseline evaluation, several studies suggest that quantification of post ablation LA scarring may play a role in determination of the AF recurrence risk.^[10]^ Several recent studies managed to assess the feasibility of LGE-MRI in detecting both pre-existing and post-ablation atrial and ventricular fibrosis.^[8,11–14]^ Their results raised interest in the use of CMR as a periprocedural risk assessment tool. Despite these promising results, the assessment of atrial and ventricular fibrosis has not yet been widely adopted in clinical practice.^[15–18]^ We should not forget that the capacity of LGE-CMR to detect fibrosis in the atria is still controversial due to the lack of reproducibility. Thus, this trial aims to validate myocardial fibrosis, targeting both atrial and ventricular fibrosis quantified by CMR, as predictor for AF recurrence.

Previous observational studies showed that elevation of several inflammatory serum biomarkers, such as hsCRP or IL-6, are associated with occurrence and recurrence of AF, since patients with AF present significantly higher levels of inflammatory biomarkers as compared with subjects maintaining sinus rhythm.^[3,19–22]^ Therefore, the role of inflammation in AF recurrence has been recently proposed as a new and challenging hypothesis to explain the high rate of recurrence after AF conversion.^[3,21,23–26]^ As the exact pathways from inflammation to AF are still unclear, it is presumed that inflammatory cytokines may bind to atrial myocytes inducing tissue damage.^[24]^ In line with this hypothesis, the FIBRO-RISK trial aims to investigate the correlation between inflammatory biomarkers and cardiac fibrosis, evaluated via LGE-CMR, in order to prove the impact of inflammatory-related myocardial fibrosis on the risk of recurrence after successful catheter ablation of AF.

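### The cardiac magnetic resonance (CMR) window permits scans after ablation, so left atrial fibrosis, a primary-objective predictor, could mix native fibrosis with fresh ablation lesion

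*Protocol article*

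**What the plan says.** Fibrosis belongs to the primary objective, which section 1.2 words as follows: "investigate the correlation between the degree of LA and LV fibrosis quantified by cardiac magnetic resonance (CMR), inflammatory biomarkers, and the risk of AF recurrence".

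The timing of the scan is described in several places:

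- The Abstract and section 2.3 measure "the amount of myocardial fibrosis at the level of left atrium and left ventricle at baseline +/− 7 days".
- Section 2.9 makes baseline day 0 and puts both the late-enhancement CMR and the catheter ablation in that visit. The CMR is listed first.
- Section 2.3 also has a sentence that begins "Imaging biomarkers and laboratory analyses such as", names four blood markers, and says that these "will be determined in the first 24 hours after the procedure". Its subject covers imaging as well as blood tests.
- Section 2.6.4, in the radiofrequency paragraph, says the electro-anatomical map will be "improved by fusing images acquired with CMR images". The cryoablation paragraph has no such step.

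On classification, section 2.6.3 uses enhancement alone: "fibrotic areas will be considered those with slow washout kinetic". The Discussion cites work on "detecting both pre-existing and post-ablation atrial and ventricular fibrosis" and so treats the two as different things.

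**The concern.** The predictor is meant for use before the procedure: the Discussion speaks of patients who are scheduled for ablation, and the evidence it cites concerns fibrosis already present at baseline. A scan a few days before ablation shows that substrate. A scan a few days after shows the substrate plus the enhancement caused by the procedure. If both enter one LA fibrosis variable, some of its variation reflects when the patient was scanned and not how much fibrosis the patient had.

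Added variation of this kind, if unrelated to outcome, pulls the difference between the recurrence and no-recurrence groups towards zero. It also cannot be repaired later, because the pre-ablation atrium cannot be imaged once the patient has been treated.

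**Working it through.** **Step 1. What the timing rules permit.**

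| Place | Rule | Scan after ablation permitted? |
|---|---|---|
| Abstract, 2.3 | Baseline ± 7 days | Yes, days +1 to +7 |
| 2.9 | CMR and ablation both on day 0, CMR listed first | Order suggested, not required |
| 2.3, 24-hour sentence | Imaging biomarkers within 24 hours after the procedure | Yes, read literally |
| 2.6.4, radiofrequency | CMR fused with the map | No, a prior scan is implied |
| 2.6.4, cryoablation | No CMR step | Silent |

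The window covers 7 + 1 + 7 = 15 calendar days, and 7 of them lie after the ablation day (7/15 = 47%). This is a count of permitted days, not an estimate of the share of scans. No sentence requires the fibrosis scan to come first.

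**Step 2. The plan's own design figure.** Section 2.12 gives 50 per group, 0.60 against 0.89, two-sided 0.05 and 90% power. A pooled two-proportion test gives 92.6% without and 88.6% with continuity correction, so the stated figure reproduces. It concerns MACE-free proportions and does not bear on scan timing.

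**Step 3. Illustration of the effect on LA fibrosis.** All inputs are assumptions except the total of 100 patients.

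- Groups of 40 with and 60 without recurrence. This applies the 60% event-free figure of section 2.12 to recurrence, in line with the 35% to 40% recurrence in the Abstract.
- True standardised difference d giving 90% power with a two-sided 5% test: d = (1.960 + 1.282) / √(40 × 60 / 100) = 3.242 / 4.899 = 0.66.
- A fraction f of scans is post-ablation. Lesion adds a shift with mean m and SD 0.5, in units of the native fibrosis SD, unrelated to outcome.

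The variance of the measured value becomes V = 1 + f × 0.25 + f(1 − f)m², and the observed difference is 0.66 / √V.

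| f | m | V | 0.66/√V | Power, noncentral t | Power, simulation (4000 runs) |
|---|---|---|---|---|---|
| 0 | – | 1 | 0.66 | 0.89 | 0.89–0.90 |
| 0.25 | 1 | 1.25 | 0.59 | 0.82 | 0.81 |
| 0.25 | 2 | 1.8125 | 0.49 | 0.66 | 0.67 |
| 0.50 | 1 | 1.375 | 0.56 | 0.78 | 0.77 |
| 0.50 | 2 | 2.125 | 0.45 | 0.59 | 0.58 |

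Formula and simulation agree to about one percentage point.

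**Step 4. Could the association reverse?** The model above only adds noise, so it can only attenuate. For the mean difference to change sign, lesion enhancement would have to be lower in recurrence patients by more than 0.66 / f: 2.64 SD at f = 0.25, or 1.32 SD at f = 0.50. Nothing in the documents supports a gap of that size.

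**The case against.** The strongest reply is that a pre-procedure scan is plainly intended. Section 2.9 lists CMR before ablation, radiofrequency cases need the images for fusion, and the Discussion is about patients awaiting ablation. On this view ± 7 days is an ordinary visit tolerance, loosely worded, in a condensed article whose flowchart is not shown.

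This limits the point without removing it. A reader might infer that lesions will be counted as fibrosis; the documents show only that they could be. But the window is a stated rule, given twice, and the 24-hour sentence points away from the order in section 2.9. The problem is conflicting text, not missing detail.

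Other stronger readings also go too far:

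- *Post-ablation scans will cluster in cryoablation patients.* The fusion step is described for radiofrequency only, so uneven error by technique is possible. No passage says cryoablation patients are scanned later, and section 2.3 has CMR assess pulmonary vein anatomy without distinguishing techniques.
- *All imaging predictors are affected.* The mechanism is enhancement in the LA wall. It does not reach left ventricular (LV) fibrosis, and no case is made for epicardial fat.
- *The power loss is an estimate.* The affected share, the lesion shift and the 0.66 are all assumed. If every radiofrequency patient is scanned beforehand, a 50% share needs at least half the cohort to be cryoablation patients scanned afterwards, and the technique mix is not given.

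**Conclusion.** The point holds for LA fibrosis. As written, the timing rules admit late-enhancement scans after ablation, and the analysis method cannot tell lesion from native fibrosis. A primary-objective predictor could therefore combine two quantities that the Discussion itself keeps apart, with attenuation as the expected direction if lesion enhancement is unrelated to outcome.

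The size is unknown. On the assumed inputs, the standardised difference falls from 0.66 to between about 0.59 and 0.45, and power from about 90% to between about 81% and 58%. A reader might go further and expect a reversed association; the calculation does not show that, and the documents do not establish that lesion extent tracks recurrence among patients who all had a successful procedure.

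**What to change.** 1. In the Abstract and section 2.3, change the CMR window for LA fibrosis to day −7 to day 0, before the ablation procedure.
2. Reconcile the 24-hour sentence in section 2.3 with section 2.9. Changing the window alone would leave section 2.3 contradicting itself on imaging.
3. State that a scan obtained after ablation does not enter the LA fibrosis predictor, or is analysed as a separate scar variable. LV fibrosis from such a scan may be kept.

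The cost is a change of wording and the scheduling of the same single scan before the procedure, with no additional imaging. The downside is that an occasional patient not scanned before ablation will have no LA fibrosis value.

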**Figure 1 F1:**
[figure not shown]
Flowchart diagram of FIBRO-RISK study. hs-CRP = high sensitivity C reactive proteine, IL-6 = Interleukine 6, LGE – CMR = late Gadolinium enhancement CMR, MMPs = matrix metalloproteinases, TTE = transthoracic echocardiography.

Inclusion criteria:

Patients with non-valvular paroxysmal or persistent AF who undergo successful catheter ablation, either by cryoablation or by radiofrequency advanced 3D mapping system;Ability to provide informed consent;Patients aged at least 18 years;

Exclusion criteria:

Patients with valvular AF;Patients with acute coronary syndrome in the last 30 days;Patients in whom AF is presumed to be caused by hyperthyreosis;Patients with long-standing persistent or permanent AF;Unwillingness or incapacity to provide informed consent;Allergy to gadolinium contrast media;Absolute or relative contraindications to magnetic resonance imaging;Pregnancy or lactation;Women with childbearing potential in absence of any contraceptive treatment;Renal insufficiency (creatinine greater than 1.5 mg/dL) or renal failure requiring dialysis;Active malignancy or malignancy within the last 5 year prior to enrollment;Conditions associated with an estimated life expectancy of under 2 years;

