## Conclusions

4

FIBRO-RISK will be the first CMR-based study that will investigate the impact of inflammation-mediated myocardial fibrosis on the risk of recurrence after successful catheter ablation of AF, aiming to validate inflammatory biomarkers and myocardial fibrosis as predictors for AF recurrence.

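### Entry is not limited to a first left atrial ablation and older infarcts are admitted, so earlier ablation lesions and infarct scar are scored as the fibrosis under study

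*Protocol article*

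**What the plan says.** The entry criteria follow Figure 1 in section 2.3 of the protocol article. The disease criterion is "Patients with non-valvular paroxysmal or persistent AF who undergo successful catheter ablation", by cryoballoon or radiofrequency. The other two inclusions are consent and age. Nothing says that the procedure must be the patient's first.

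The only coronary exclusion is "Patients with acute coronary syndrome in the last 30 days". None of the other printed exclusions concerns previous ablation or an older infarct.

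Section 2.6.3 measures atrial and ventricular fibrosis by LGE cardiac magnetic resonance (CMR). It states that "fibrotic areas will be considered those with slow washout kinetic". It gives no rule on location or pattern that would separate an ablation line or an infarct from other enhancement.

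Section 2.13 lists the *t* test, the Mann-Whitney test and the Fisher exact test, and no adjusted analysis. Section 4 says that the study will "investigate the impact of inflammation-mediated myocardial fibrosis on the risk of recurrence after successful catheter ablation of AF". The abstract and section 2.1 use the same mechanistic language. Baseline medical history is taken (2.6, 2.9, 2.11), but no use of it in eligibility or analysis is stated beyond the criteria above.

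**The concern.** LGE does not show what caused an enhanced area. Two groups of patients admitted by 2.3 have enhancement from a known other source.

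- **Repeat ablation.** The left atrium carries lesions from the earlier procedure, and these patients have probably relapsed at least once. If they are also likelier to relapse again, LGE and recurrence are linked through the earlier ablation. The unadjusted comparison would show this as an effect of fibrosis, so the bias is towards a false positive.
- **Infarct older than 30 days.** The ventricular scar is ischaemic but is scored as left ventricular fibrosis. If it is equally common in both recurrence groups it adds noise and can hide a real difference. If not, it biases the comparison.

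At stake is whether an association, or its absence, can be read as evidence about inflammation-mediated fibrosis. This is separate from the timing of CMR around the index ablation: a scan before the index procedure still shows lesions from an earlier one.

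**Working it through.** The plan gives no figure on this point, so there is none to reproduce. The text check comes first, then an illustration of size.

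**Text check.** An earlier ablation or an older infarct passes every printed criterion in 2.3. Enhancement from either meets the definition in 2.6.3. No method in 2.13 removes it.

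**Repeat ablation: inputs.** From the documents: 100 patients (2.12), and recurrence of 35% to 40% (abstract), taken as 38%. Assumed, because the documents are silent: repeat share *r* = 10% or 20%; relapse in repeats *p* = 50% or 60%, with overall relapse held at 38%; LGE shift *k* = 1 or 2 SD of the uncontaminated measure; no effect of native fibrosis.

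**Formulas.**
- Share of repeats among recurrers: f1 = r·p/0.38. Among non-recurrers: f2 = r·(1 − p)/0.62.
- Spurious mean difference: d = k·(f1 − f2).
- Within-group variance: s² = 0.38·[1 + k²·f1(1 − f1)] + 0.62·[1 + k²·f2(1 − f2)].
- Expected test statistic with 38 and 62 patients: (d/s)·√(38·62/100) = 4.854·d/s. The positive rate is the probability beyond ±1.96.

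**Lowest scenario** (r = 0.10, p = 0.5, k = 1): f1 = 0.132, f2 = 0.081, d = 0.051, s = 1.044, d/s = 0.049. Expected statistic 0.24, positive rate 5.6%.

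**Highest scenario** (r = 0.20, p = 0.6, k = 2): f1 = 0.316, f2 = 0.129, d = 0.374, s = 1.268, d/s = 0.295. Expected statistic 1.43, positive rate 29.8%.

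| r | p | k | d | d/s | positive rate |
|---|---|---|---|---|---|
| 0.10 | 0.5 | 1 | 0.05 | 0.05 | 5.6% |
| 0.10 | 0.5 | 2 | 0.10 | 0.09 | 7.1% |
| 0.10 | 0.6 | 1 | 0.09 | 0.09 | 7.2% |
| 0.10 | 0.6 | 2 | 0.19 | 0.16 | 12.2% |
| 0.20 | 0.5 | 1 | 0.10 | 0.09 | 7.5% |
| 0.20 | 0.5 | 2 | 0.20 | 0.16 | 12.1% |
| 0.20 | 0.6 | 1 | 0.19 | 0.17 | 13.5% |
| 0.20 | 0.6 | 2 | 0.37 | 0.29 | 29.8% |

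A simulation of 4,000 studies of 100 patients per scenario agrees within about one percentage point. The scale matters: d is in SDs of the uncontaminated measure, while the *t* test works with the within-group SD. On that scale the maximum is about 0.3, not 0.37.

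**Old infarct: dilution.** Take 40 recurrers and 60 non-recurrers, from the 60% event-free assumption in 2.12. A true difference of (1.960 + 1.282)·√(1/40 + 1/60) = 0.66 SD has 90% power. If a share *f* in both groups carries scar worth *k* SD, the SD becomes √(1 + k²·f(1 − f)). With f = 0.10 and k = 1 the SD is 1.044 and power is 87%. With f = 0.30 and k = 2 the SD is 1.356 and power is 67%. Both *f* and *k* are assumed.

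**The case against.** The primary objective in 1.2 names left atrial and left ventricular fibrosis quantified by CMR. It says neither native nor inflammation-mediated, and infarct scar is left ventricular fibrosis on CMR. Section 3 also presents the markers as a prediction panel for patients scheduled for ablation, and broad entry suits that purpose. This stands: a reader might infer that the study cannot measure its primary objective, and the documents do not support that. The problem lies in the mechanistic reading given in the abstract, 2.1 and 4, and in the bias that repeat patients can bring to the recurrence comparison.

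A reader might also infer that chronic inflammatory disease or anti-inflammatory treatment should exclude patients. The documents do not support this. The abstract defines the serum markers as measures of systemic inflammation, and they do not enter the LGE measure, so such inflammation is not counted as fibrosis.

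Section 3 should not be overread either. It reports that other studies managed to "assess the feasibility of LGE-MRI in detecting both pre-existing and post-ablation atrial and ventricular fibrosis", and then calls atrial LGE controversial because of poor reproducibility. That supports the possibility that old lesions are seen, not that they always are.

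The prevalence, shift and relapse values are assumptions, and the lowest scenario is harmless. Figure 1 and section 2.4 are not shown, so a further criterion there cannot be ruled out, although the lists in 2.3 read as complete. A sensitivity analysis could sit in an analysis plan that is not shown, but eligibility is fixed in this document.

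**Conclusion.** The point holds for previous ablation and previous infarct. As printed, 2.3 admits both, 2.6.3 scores their enhancement as fibrosis and 2.13 does not remove it. Previous ablation matters more, because it can create a false association; old infarct scar mainly clouds the interpretation of left ventricular fibrosis and may cost power.

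The gap in the text is clear, but its size is unknown. Under the assumed ranges, the false-positive rate of the left atrial comparison runs from about 6%, which is negligible, to about 30%, which is serious, with a spurious difference of at most about 0.3 within-group SD. If few or no repeat procedures are enrolled, the left atrial problem disappears.

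**What to change.** In 2.3, restrict entry to a first left atrial ablation. If repeat patients are to be kept, or are already enrolled:

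- flag prior left atrial ablation and prior myocardial infarction for every patient from the medical history already collected, as explicit database items;
- make the left atrial fibrosis comparison in patients without prior ablation, and the left ventricular fibrosis comparison in patients without prior infarct;
- report the full cohort alongside, with the number in each flagged group.

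Excluding every patient with a previous infarct is not needed. The study runs from January 2019 to December 2020 with 12-month follow-up, which leaves about 24 − 12 = 12 months to enrol 100 patients at one centre.

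The cost is a slightly smaller eligible pool or analysis set, and no new procedure. If 10% to 20% of patients leave the left atrial comparison and the 40:60 split is unchanged, the difference detectable with 90% power rises from 0.66 SD to 0.66·√(100/90) = 0.70 or 0.66·√(100/80) = 0.74 SD of the uncontaminated measure.
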